### Blinding

The participant and the respective operators providing treatment could not be blinded due to the nature of the intervention. During T_1_, T_2_, or any emergency appointments, laceback complications are first assessed by the principal investigator. This is not blinded, as it is to merely record how many laceback complications occur on the side that has laceback, whereas the contralateral side does not have any laceback. The principal investigator then removes the laceback ligatures. Then, archwire complications and plaque scores are assessed by an orthodontic resident not treating the participant. As such, data collection for archwire complications and plaque scores will be blinded. As the lacebacks are removed by the principal investigator, the assessor is unaware of the site of intervention.

Examiner calibrations were conducted prior to trial commencement for plaque score assessment to ensure good inter- and intrarater reliability among all plaque score assessors. All data are coded and anonymized by the coinvestigator who withholds coding information about treatment allocation from the main data analyst until major analyses are completed. Unblinding is also allowed if a participant withdraws from the trial due to a severe adverse event. The overall study flow is illustrated in Figure 5.

**Figure 5. F5:**
[figure not shown]
Overall study flow.

### Intended Statistical Analysis

Statistical analysis is conducted using IBM SPSS Statistics (version 31). Descriptive statistics are used to report participant demographics, baseline characteristics, and frequency of laceback complications. To assess whether the data are normally distributed, interpreting the shape of the histogram and the Shapiro-Wilk test are used. Intra- and interrater reliability for plaque score assessment are measured using Cohen kappa. The threshold for good inter- and intrarater reliability is set to be more than 0.8.

Repeated outcome measurements of plaque scores will be analyzed using a mixed model for repeated measures. The model includes treatment group, time, and treatment-by-time interaction as fixed effects, with participant included as a random effect. A mixed model for repeated measures allows inclusion of participants with incomplete follow-up data without requiring formal imputation, assuming data are missing at random. If the data are not normally distributed, plaque scores over time (T_0_, T_1_, and T_2_) will be compared using the Friedman test.

From the pain diary gathered, the pain scores are plotted against time to allow calculation of area under the curve (AUC) using the trapezoidal rule [34]. Pain AUC will be calculated between T_0_ and T_1_ and T_1_ and T_2_. The mean pain AUC for laceback and no laceback sides will be calculated by averaging pain AUC values between T_0_ and T_1_ and between T_1_ and T_2_. To compare differences in mean pain AUC of laceback and no laceback groups, a paired *t* test is used if data are normally distributed. If the normality assumption is violated, the Wilcoxon signed-rank test is applied instead.

The mean frequency of archwire complications is recorded by summing up the number of complications that happen throughout the study period from T_0_ to T_2_. To compare differences in the mean frequency of archwire complications between the laceback and no laceback groups, a paired *t* test is used if data are normally distributed. The mean frequency of laceback complications and the number and percentage of participants with at least 2 laceback complications are also reported. The value of *P*<.05 is considered statistically significant.

Sensitivity analysis will be conducted by comparing the results of intention-to-treat and per-protocol analyses. If both analyses yield similar results, this demonstrates the robustness and validity of the study’s conclusions.

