## Methods

### Study Design

This is a single-center, single-blind, split-mouth randomized controlled trial with a 1:1 allocation ratio for the 2 groups (left and right sides of the oral cavity). In this study, either the left or right side of each participant’s oral cavity is randomly assigned to receive a laceback, while the contralateral side serves as the control (no laceback). The study is aimed to fulfill as many items as possible in the CONSORT (Consolidated Standards of Reporting Trials) 2025 checklist for reporting randomized controlled trials, and the SPIRIT (Standard Protocol Items: Recommendations for Interventional Trials) 2025 checklist for preparing protocols of randomized controlled trials [18,19].

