**Orthodontic factors**
Full upper and lower arch orthodontic fixed appliance.Extraction of bilateral upper and lower permanent first or second premolars at least 2 weeks before bond-up.No previous orthodontic treatment.
**
*Exclusion criteria*
**
Craniofacial deformities.Mental or physical disability leading to impaired manual dexterity and difficulty comprehending and following oral hygiene instructions.Underlying chronic medical illness, oral diseases.
**
*Withdrawal criteria*
**
Participants are free to withdraw anytime during the period of study. Reasons for withdrawal will be noted down. Possible criteria of withdrawal include:Serious adverse events arising from laceback, which is very unlikely as it has not been reported in literature.Participant not following study procedures.Participant unwilling to continue orthodontic treatment.

An intention-to-treat analysis is used, whereby data from all participants is analyzed irrespective of any subsequent withdrawal or protocol deviation to ensure that the results will reflect the effects of laceback in a real-world setting, while maintaining the study power because no participants are omitted from the analysis [20,21]. Repeated measures data for plaque score and pain score will be analyzed using a mixed model for repeated measures (MMRM), which accounts for within-participant correlation and handles missing data without formal imputation under the missing at random assumption [22].

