### Sample Size Calculation

The sample size is determined using G*Power (Version 3.1.9.6, Heinrich Heine University, Düsseldorf, Germany). To assess the effect of laceback on a patient’s oral hygiene, a previous split-mouth study using the Orthodontic Plaque Index (OPI) to record plaque score on orthodontic patients will be used in this study [23]. By referring to the SEM and sample size (n) reported in that study, the SD of OPI is calculated to be 1.88 by applying the formula $SD=SEM\times \sqrt{n}$. A difference of 1 point in OPI was deemed clinically meaningful to be detected. A total of 34 participants are needed for 68 sites (34 laceback and 34 no laceback), which would give a power of 85% with a significance level of 0.05 to detect a 1-unit difference in OPI score. Assuming a 10% dropout rate, 38 participants are recruited, providing a total of 76 sites (38 laceback and 38 no laceback).

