**Figure 4. F4:**
[figure not shown]
Criteria for Orthodontic Plaque Index scores.OPI: Orthodontic Plaque Index.

Plaque score is recorded on the laceback and no laceback side during T_0_ (before laceback placement during first review appointment 1 wk after bond-up) as baseline, T_1_ (4 wks after laceback placement), and T_2_ (4 wks after T_1_). Once intervention starts at T_0_, if a participant cannot attend T_1_ or T_2_ appointments, a maximum of 2 weeks’ leeway is given, corresponding to the normal orthodontic follow-up interval of 6 weeks between appointments.

During T_0_, T_1_, and T_2_, archwires and lacebacks (if present) are removed, and plaque disclosing agent (GC Tri Plaque ID Gel; GC Asia Dental) is applied on the buccal surfaces of upper and lower canines, premolars, and first molars. Then, plaque score is recorded on those teeth by a blinded clinician not involved in the treatment of the participant. The tooth surface adjacent to each side of the bracket (mesial, distal, occlusal or incisal, and gingival) is visually examined for accumulation of plaque. The average OPI for the laceback and no laceback side is calculated by adding up the plaque score of all the teeth recorded on each side and dividing it by the number of teeth scored. The maximum plaque score for each side is 4, and the minimum score is 0. The criteria for scoring are explained in Figure 4 [32].

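### The primary plaque model states only a participant random effect for six scores per mouth; if sides differ persistently its standard errors are wrong, in a direction that depends on the contrast

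*Protocol article*

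**What the plan says.** Under Study Design, the article describes a "split-mouth randomized controlled trial with a 1:1 allocation ratio for the 2 groups (left and right sides of the oral cavity"), so the randomised unit is a side of the mouth. Under Primary Outcome: Plaque Score, "Plaque score is recorded on the laceback and no laceback side during T_0", and again at T1 and T2. Tooth scores are averaged within each side, which leaves one OPI value per side per visit and six per participant.

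Under Intended Statistical Analysis, "Repeated outcome measurements of plaque scores will be analyzed using a mixed model for repeated measures", and the structure is given as "The model includes treatment group, time, and treatment-by-time interaction as fixed effects, with participant included as a random effect". The intention-to-treat paragraph after the eligibility textbox describes the same method as one "which accounts for within-participant correlation and handles missing data without formal imputation under the missing at random assumption". Neither place mentions a side level, a participant-by-visit term or a residual covariance structure. Neither says which model term or contrast is the primary test.

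**The concern.** A participant intercept with independent residuals gives all six scores in a mouth one common correlation. The unit that receives the treatment, side within participant, has no variance of its own. The error term then pools side-to-side variation, shared visit-to-visit variation and pure residual noise, and applies that single figure to every contrast.

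Contrasts that depend on how stable sides differ (the treatment effect averaged over visits) can receive a standard error that is too small. Contrasts in which stable side differences cancel (change from T0, the treatment-by-time interaction) can receive one that is too large. This is the only primary outcome. Because the article does not name the decisive contrast, a reader cannot tell whether the risk is false positives or lost power.

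Persistent side differences fit the trial's own reasoning. The minimization balances premolar extraction type and side of allocation between the arms, and these features stay with a side through all three visits.

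**Working it through.** **Inputs from the article.** Two sides, three visits, 34 evaluable participants, 38 recruited, target difference 1 OPI point, SD 1.88, 85% power, significance level 0.05.

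**Inputs not in the documents (assumed).** With residual variance s_e² = 1, side-within-participant variance s_v² is taken from 0 to 1, and participant-by-visit variance s_pv² is 0 or 0.5.

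**Step 1: the plan's own figure.** For the sample size, "the SD of OPI is calculated to be 1.88 by applying the formula". A two-sided paired t test with standardised difference 1/1.88 = 0.532 needs n = 34 (power 85.3%), and 34/0.9 = 37.8, rounded up to 38. This reproduces the stated numbers. A one-sided paired test would need 27, and two independent means would need 64 per arm. The sample size is therefore already a paired-side calculation.

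**Step 2: the error variance of the stated model.** Take score = participant + side within participant + participant-by-visit + residual. With complete data there are five within-mouth degrees of freedom per participant:

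- one for the side difference averaged over visits, expectation s_e² + 3s_v²
- two for visits, expectation s_e² + 2s_pv²
- two for side by visit, expectation s_e²

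The participant-only model pools them: M = s_e² + (3/5)s_v² + (4/5)s_pv², on 5(n − 1) = 165 df when n = 34.

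**Step 3: model variance against true variance of the side difference.**

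| Contrast | Model | True | (Model SE / true SE)² |
|---|---|---|---|
| Averaged over T0, T1, T2 | 2M/(3n) | 2(s_e² + 3s_v²)/(3n) | M/(s_e² + 3s_v²) |
| Averaged over T1, T2 | M/n | (s_e² + 2s_v²)/n | M/(s_e² + 2s_v²) |
| Single visit | 2M/n | 2(s_e² + s_v²)/n | M/(s_e² + s_v²) |
| Change from T0 | 4M/n | 4s_e²/n | M/s_e² |

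n cancels from every ratio, so using 38 instead of 34 changes only the degrees of freedom.

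**Step 4: results.** Each cell gives the SE ratio, then type I error at nominal 5%, n = 34. Error rates come from 20,000 simulated trials per row, except the T1–T2 column, which uses the approximation 2Φ(−t × ratio), with t the 97.5% point on 165 df.

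| s_v² | s_pv² | M | All visits | T1–T2 | Single visit | Change from T0 |
|---|---|---|---|---|---|---|
| 0 | 0 | 1.00 | 1.00, 4.9% | 1.00, 4.8% | 1.00, 5.1% | 1.00, 5.3% |
| 0.25 | 0 | 1.15 | 0.81, 11.6% | 0.88, 8.4% | 0.96, 6.2% | 1.07, 3.6% |
| 0.5 | 0 | 1.30 | 0.72, 15.6% | 0.81, 11.1% | 0.93, 6.9% | 1.14, 2.6% |
| 1 | 0 | 1.60 | 0.63, 21.4% | 0.73, 14.9% | 0.89, 8.2% | 1.26, 1.5% |
| 0.5 | 0.5 | 1.70 | 0.82, 10.2% | 0.92, 6.9% | 1.06, 3.7% | 1.30, 1.1% |
| 1 | 0.5 | 2.00 | 0.71, 16.6% | 0.82, 10.7% | 1.00, 5.1% | 1.41, 0.5% |

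The 2-df interaction test falls to 3.4%, 2.0% and 1.0% in the second to fourth rows. A REML fit of the stated model (60 replicates) agrees. At s_v² = 1 and s_pv² = 0, the mean SE was 0.301 for a single visit and 0.426 for change from T0, against a true value of 0.343 for both.

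**Step 5: where the errors cancel.** Setting each ratio to 1:

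- Single visit: 0.6s_v² + 0.8s_pv² = s_v², so 0.4s_v² = 0.8s_pv². The last row of the table is such a case.
- Averaged over all visits: 0.8s_pv² = 2.4s_v², so s_pv² = 3s_v².
- Change from T0: the ratio equals 1 only when both variances are zero.

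**Step 6: the correct analysis.** Testing the per-mouth side difference gave simulated type I error of 4.9–5.2% for every contrast in every simulated scenario.

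**The case against.** The strongest reply is that the article does not rule out a further covariance structure. The label mixed model for repeated measures usually goes with one, SPSS sets residual covariance separately from random effects, and Clinical Trial Registration points to an analysis plan that is not shown. This has some force: an intended structure that separates sides would meet much of the point and could be stated in a sentence. It does not dispose of the point, because the article goes beyond the label. It writes out the fixed and random parts, and the only dependence it describes is within participant.

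Second, the size rests on variances that the documents do not give. That stands. A reader might infer that the standard error is wrong in any event, or that the trial's false-positive rate is 21%. Neither follows. With no side and no participant-by-visit variance there is no error. The 21% needs side variance equal to residual variance, and it belongs to an effect averaged over all visits, which the article does not name as its primary test.

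Third, a reader might infer that only an absence of side variation makes the model valid. Step 5 shows otherwise for single-visit and averaged contrasts.

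Fourth, with complete balanced data the estimated treatment differences are unaffected. That is correct. The fault lies in their standard errors and tests.

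**Conclusion.** The point holds in conditional form. As written, the primary model cannot tell same-side from opposite-side scores. If sides differ persistently, its standard errors are biased in a direction set by the contrast.

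For side variance of 0.25 to 1 times residual and no participant-by-visit variance, type I error is about 11–21% for the effect averaged over visits, 6–8% for a single visit, and 3.6% down to 1.5% for change from T0. Participant-by-visit variance pushes the change contrast further towards lost power and can offset the other two errors in part or in full. These ranges rest on assumed variances and complete data.

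Nothing here calls the sample size into question: 34 and 38 already match a paired test. The specification should be corrected before analysis, because it governs the only primary outcome and the article leaves the decisive contrast open.

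**What to change.** Use one of two specifications, with Satterthwaite or Kenward-Roger degrees of freedom:

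1. Analyse the laceback-minus-no-laceback difference at each visit in a repeated-measures model with visit as a fixed effect and an unstructured covariance over visits. Participant and participant-by-visit effects cancel in the difference.
2. Keep the stated model and add random effects for side within participant and for participant by visit.

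These are not identical: the second assumes equal variances and equal correlations of the side differences over visits, and the first does not. Adding side within participant alone is not enough. The four remaining degrees of freedom would then pool to [2(s_e² + 2s_pv²) + 2s_e²]/4 = s_e² + s_pv², so the change contrast would still have too large a standard error whenever s_pv² is above zero.

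Name the primary test as a post-baseline contrast or change from T0. The treatment effect averaged over all visits should not serve, because T0 is scored before the laceback is placed.

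The cost is one or two model terms and a sentence naming the contrast, with no new data and no change in sample size. Primary analysis is scheduled for October 2027, and allocation coding is withheld from the main data analyst until the major analyses are complete, so the change can still be made as a credible prespecification.

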**Methods:**

This is a single-center, single-blind, split-mouth randomized controlled trial conducted at the Orthodontic Clinic, International Islamic University Malaysia. Eligible participants are patients aged 15 years and older, medically fit with Basic Periodontal Examination scores of 0‐2, requiring full fixed appliance treatment with bilateral premolar extractions and no prior orthodontic treatment. Those with craniofacial deformities, systemic illness, or disability affecting oral hygiene compliance are excluded. Each participant’s oral cavity is randomly allocated using a minimization method, so that one side receives a passive 0.010-inch stainless-steel laceback from the first molar hook to the canine bracket, while the contralateral side receives identical standard fixed appliance treatment (McLaughlin, Bennett, and Trevisi prescription brackets, 0.014-inch superelastic nickel-titanium archwires, and elastomeric modules) without laceback. Outcomes are assessed at baseline (T0), 4 weeks (T1), and 8 weeks (T2) after laceback placement. The primary outcome is the orthodontic plaque index. Secondary outcomes include archwire and laceback complication frequencies and pain assessed by visual analog scale area under the curve. A total of 38 participants provided 85% power to detect a 1-unit orthodontic plaque index difference (*α*=.05). Mixed-model repeated-measures analysis is applied to plaque scores; paired parametric or nonparametric tests to other outcomes. Plaque and archwire assessors are blinded to treatment allocation.

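### The primary plaque model, as listed, implies that the pre-placement T0 score is an outcome visit; a treatment main effect read from it would estimate only two thirds of a constant laceback effect

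*Protocol article*

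**What the plan says.** The Intended Statistical Analysis section states: "Repeated outcome measurements of plaque scores will be analyzed using a mixed model for repeated measures". On the model terms it says "The model includes treatment group, time, and treatment-by-time interaction as fixed effects", "with participant included as a random effect". No baseline covariate is listed, and no term, visit or contrast is named as the primary test.

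The mixed-model sentences list no visits. The visits appear in the non-normal fallback of the same paragraph: "plaque scores over time (T_0_, T_1_, and T_2_) will be compared using the Friedman test". The Abstract gives the same three times: "Outcomes are assessed at baseline (T0), 4 weeks (T1), and 8 weeks (T2) after laceback placement".

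Under Primary Outcome: Plaque Score, T0 is described as "before laceback placement during first review appointment 1 wk after bond-up) as baseline". T1 follows four weeks after placement and T2 four weeks after T1.

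The Sample Size Calculation is built on one difference that is tied to no visit: "A difference of 1 point in OPI was deemed clinically meaningful to be detected". It uses an SD of 1.88, 85% power and a significance level of 0.05, giving 34 participants, or 38 after 10% dropout.

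**The concern.** The side that receives the laceback is randomised and T0 is scored before placement, so the expected side difference at T0 is zero. If T0 is one of three response visits, the marginal treatment effect is an average over a visit with no effect and two visits that may have one. It then no longer estimates the quantity that the sample size was built on.

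The consequence is a matter of estimation as well as power. A true effect equal to the protocol's own clinically meaningful difference of 1 point would be reported as a value below that threshold. The T0 score would also be spent as an outcome instead of being used to sharpen the follow-up comparison.

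**Working it through.** **Inputs.** From the Sample Size Calculation: difference 1 OPI unit, SD 1.88, alpha 0.05, power 85%, 34 participants. From the plaque-outcome section: T0 before placement, T1 and T2 after it. Assumed because the protocol does not give it: the correlation r of the within-participant side difference between any two visits, taken as equal for all pairs and varied from 0 to 1.

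**Step 1: the plan's own figure.** A two-sided paired t test with difference 1 and SD of the difference 1.88 needs n = 34 and has power 0.853. With 10% dropout, 34 / 0.9 = 37.8, so 38. The stated numbers reproduce, with 1.88 serving as the SD of a single paired difference.

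**Step 2: what each estimate targets.** Let the side differences at T0, T1 and T2 be (0, d, d).
- Main effect over three equally weighted visits: (0 + d + d) / 3 = 2d/3. With d = 1 this is 0.667. In 300 simulated data sets the average was 0.672, and a mixed-model fit to one of them confirmed that the main effect equals the plain average of the three side differences.
- T2 contrast: d = 1 (simulation 1.00).
- Mean of T1 and T2, minus T0: d = 1 (simulation 1.00).
- If the effect is present only at T2, the main effect is (0 + 0 + d) / 3 = d/3.

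**Step 3: power at n = 34.** The comparison is a paired test on each participant's averaged side difference.
- Three-visit average: effect 2/3, SD = 1.88 × √((1 + 2r)/3).
- T1-T2 average: effect 1, SD = 1.88 × √((1 + r)/2).
- Noncentrality = effect / SD × √34.

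Example, r = 0.5: the three-visit SD is 1.88 × √(2/3) = 1.535, giving 0.667 / 1.535 × 5.831 = 2.53 and power 0.69. The T1-T2 SD is 1.88 × √0.75 = 1.628, giving 1 / 1.628 × 5.831 = 3.58 and power 0.935.

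| r | Three-visit main effect | T1-T2 average | Single visit | n for 85% power, main effect |
|---|---|---|---|---|
| 0 | 0.935 | 0.989 | 0.853 | 26 |
| 0.3 | 0.785 | 0.962 | 0.853 | 41 |
| 0.5 | 0.691 | 0.935 | 0.853 | 50 |
| 0.7 | 0.612 | 0.904 | 0.853 | 60 |
| 0.9 | 0.547 | 0.870 | 0.853 | 69 |
| 1 | 0.519 | 0.853 | 0.853 | 74 |

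**Step 4: is the T1-T2 average always better?** The squared noncentrality of the three-visit term relative to the T1-T2 average is (4/9) × [3/(1 + 2r)] × [(1 + r)/2] = (2/3)(1 + r)/(1 + 2r). This falls from 2/3 at r = 0 to 4/9 at r = 1, so under this model adding T0 to the average always loses information. Against a single visit the squared ratio is (4/3)/(1 + 2r), which exceeds 1 when r is below 1/6. At such low correlations the three-visit term has more power than a T2 contrast, although its estimate is still two thirds of the effect.

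**Step 5: what T0 could add as a covariate.** Adjustment multiplies the variance of the follow-up side difference by 1 − ρ², where ρ is its correlation with the T0 side difference. The reduction is nil at ρ = 0, 16% at 0.4 and 36% at 0.6. These values of ρ are assumptions.

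**The case against.** A reader might infer that the plan commits to a diluted primary result. The document does not support that. No sentence makes the treatment main effect the primary test. The listed interaction makes T1, T2 and change-from-T0 contrasts estimable, and none of these is diluted; nor is a treatment coefficient coded with T2 as the reference visit. T0 as a response is also an inference: the mixed-model sentences name no visits. It is the natural inference, since T0 appears in the visit list of the same paragraph and nowhere as a covariate.

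A reader might also infer that power falls to 52-69%. That range holds only if the T1-T2 average is the quantity with 85% power. The protocol uses one SD and one difference, which reads most simply as a single visit, and on that basis the range is 52-94%. Nor is the power statement at odds with every test the model offers, because it fits a T1 or T2 contrast.

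The missing primary contrast would not be a finding by itself. The article says that the intended analysis plan is on the registry, and that plan, not shown here, may name it. Allocation codes are also withheld from the main data analyst until the major analyses are done, which limits choice after the fact.

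Finally, the gain from T0 is uncertain. Differences between people already cancel in a split-mouth comparison, so only the correlation of side differences counts, and the scaling done before placement at T0 may weaken it. A covariate model would also leave out anyone without follow-up, which sits badly with the intention-to-treat statement.

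All of this stands. It makes the harm conditional. It does not make a three-visit model without a stated role for T0 a good choice when a better use of the same data costs nothing.

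**Conclusion.** The point holds in conditional form. The model as listed implies that a pre-placement score is an outcome visit. If the marginal treatment term is read as the result, it estimates 2/3 of an effect that is equal at T1 and T2, or 1/3 of an effect present only at T2. The one-third dilution does not depend on the unknown correlation. The power consequence does: 0.94 to 0.52 at n = 34, against 0.99 to 0.85 for the T1-T2 average. Both ranges assume that 1.88 is the SD of a single-visit side difference, that visits are equally correlated, and that the standard error reflects the paired side differences. The stated sample size itself reproduces. This is a worthwhile improvement to the analysis wording and not proof that the primary result will be biased.

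**What to change.** State the role of T0 and take the effect from T1 and T2 only, in one of two ways:
- T1 and T2 as the response visits, with T0 OPI as a covariate (own-side T0 plus the participant's mean T0); or
- T0, T1 and T2 as responses, with the two side means at T0 constrained equal. This also retains participants without follow-up, in line with the intention-to-treat statement under Study Participants.

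Name one primary estimate: laceback minus no laceback at T2, or averaged over T1 and T2, in OPI units with a 95% confidence interval. Make the other visit and the interaction secondary. If the registered analysis plan already does this, the article's wording need only be aligned with it.

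The cost is analysis wording; no data collection changes. If the covariate form is chosen, the statement that no participants are omitted must be reconciled with it. The article reports 24 enrolled and 14 completed, with the primary analysis due by October 2027, so the choice can still be fixed before the allocation code is opened. No particular gain in precision should be promised, since the correlation between T0 and follow-up side differences is not given.
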